### Design

The metformin study is a multicentre study, divided in two parts, both of 18 months. The first part is a randomized, double-blind placebo controlled trial, with two parallel groups. At study entry, participants are randomized to metformin or placebo for 18 months. All participants will be offered a lifestyle intervention program. This program consists of supervised physical training twice weekly, and individual dietary advice during hospital visits. Participants will visit the hospital 9 times during this part of the study. Between these visits, monthly telephone calls are made.The second part of the study is an open label, follow-up study. Participants who remain obese and insulin-resistant at entrance of the second part, can choose between metformin treatment and no medication. Participants who do not meet these criteria, do not use medication in this part of the study. Therefore, after the follow-up study there are four arms: participants with metformin in both parts, metformin in part 1 and no medication in part 2, placebo in part 1 and metformin in part 2, and placebo in part 1 and no medication in part 2 (Figure 
1).

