**Figure 1 F1:**
[figure not shown]
METFORMIN study flowchart.

During part 2, no supervised physical training is offered. Participants using Metformin will visit the hospital six times, participants not using medication will have three hospital visits and three phone calls. Participants using Metformin are seen more frequently to monitor potential adverse events.

The study protocol has been approved by the Medical Ethical Committee of the St Antonius Hospital, Nieuwegein, the Netherlands. The study is registered in the Clinical Trials register (ClinicalTrials.gov number
NCT01487993).

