### Efficacy of metformin

To assess the effect of metformin versus placebo, the Students T test will be used to compare means of normally distributed data and the Mann-Whitney U test to compare nonparametric data. The χ^2^ test will be used for dichotomous outcomes (the development of impaired fasted glucose, impaired glucose tolerance, T2DM, and the presence of micro- and macro- vascular complications versus the study groups).General linear models (analysis of repeated measures) or mixed models (if too much data is missing) will be used to determine the therapeutic effect of the drug. After part 2 of the study, comparisons will be made between the four subgroups (metformin in part 1 and part 2; metformin in part 1 and no medication in part 2; placebo in part 1 and metformin in part 2; placebo in part 1 and no medication in part 2) (Figure 
1).

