### Limitations of the study

The major limitation of our study is in the open-label, second part of the study. In this part, participants who are still eligible for receiving metformin, i.e., who remain insulin resistant and obese, may choose between taking the drug or not. This will provide a bias in the second part of the study, as participants motivated to lose weight are more likely to choose metformin compared to non-motivated participants. Possibly, this will cause an overestimation of the efficacy of metformin during the second part off the study. This will be taken into account when analysing the results of the second part of the study. The open label construction will not influence adverse reactions to the drug, therefore making it possible to draw firm conclusions about the 36-month safety and tolerability of metformin.

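### The part 2 four-subgroup comparison pools participants who no longer meet the continuation criteria with eligible decliners, so users and non-users of metformin differ through the outcome variables themselves, a selection the limitations section does not mention

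*Protocol article*

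**What the plan says.** All references are to the Protocol article.

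- **Design**, who may choose: "Participants who remain obese and insulin-resistant at entrance of the second part, can choose between metformin treatment and no medication".
- **Design**, everyone else: "Participants who do not meet these criteria, do not use medication in this part of the study".
- **Design**, resulting groups: "Therefore, after the follow-up study there are four arms". They are the four combinations of part 1 treatment and part 2 medication. Eligibility at the end of part 1 is not a factor.
- **Efficacy of metformin**, the part 2 analysis: "comparisons will be made between the four subgroups".
- **Primary endpoints and measures** and **Quaternary outcome measures**: 36-month efficacy uses measures similar to the primary ones (BMI-SDS and HOMA-IR), plus the percentages developing impaired fasting glucose, impaired glucose tolerance and type 2 diabetes.
- **Limitations of the study**: the one source of bias named is motivation, "as participants motivated to lose weight are more likely to choose metformin compared to non-motivated participants". The direction given is "Possibly, this will cause an overestimation of the efficacy of metformin during the second part off the study". The remedy is "This will be taken into account when analysing the results of the second part of the study", with no method.

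**The concern.** Two different processes put a participant in a no-medication group: declining metformin while still eligible, or no longer meeting both criteria. Only the first is a choice. The second is decided by BMI-SDS and HOMA-IR at the end of part 1, which are the variables then compared at 36 months. The metformin groups contain nobody of the second kind. A difference between users and non-users is therefore expected even if the drug does nothing.

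This selection can act in different directions. On 36-month levels, and probably on the dichotomous glucose outcomes, the lower-risk participants sit only in the no-medication groups, so users look worse. On change from the end of part 1, users were selected for a high value at that visit and tend to fall back, while those below the cut-off tend to rise, so users look better. Selection also depends on the part 1 result: the better metformin works in part 1, the more of its responders move into the group with metformin first and no medication afterwards.

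At stake is the fourth stated objective, long-term efficacy at 36 months. The limitations section would lead a reader to discount the result in one direction only.

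**Working it through.** The article gives no part 2 sample size, effect size, recovery rate or uptake, so there is no stated figure to reproduce. The check has an exact part and an illustrative part.

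**1. Decomposition (exact).** Let U, D and R be the mean outcomes of users, eligible decliners and participants no longer meeting both criteria, and w the share of R in the no-medication group. Then

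U − [wR + (1 − w)D] = (U − D) + w(D − R).

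The first term is the drug effect plus the motivation bias that the limitations section describes. The second is eligibility selection, which that section does not mention. It vanishes only if w = 0 or D = R.

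**2. Size of w.** If a fraction r no longer meets the criteria and a fraction c of the eligible choose metformin, w = r / [r + (1 − r)(1 − c)]. Both r and c are assumptions.

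- r = 0.20, c = 0.30: 0.20 / (0.20 + 0.56) = 0.26
- r = 0.35, c = 0.50: 0.35 / (0.35 + 0.325) = 0.52
- r = 0.50, c = 0.70: 0.50 / (0.50 + 0.15) = 0.77

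**3. Simulation for HOMA-IR with no drug effect.** From the document: entry at HOMA-IR 3.4 or above (Table 1), assumed to apply again at week 73; weeks 0, 73 and 146; planning difference 1.6 (Sample size). Assumed: log-normal HOMA-IR with population median 3.2 or 4.0, SD of log HOMA-IR 0.45 or 0.55, within-person correlation 0.4 or 0.7, 5% no longer obese, half of the eligible choosing metformin. A second run adds motivation m, standard normal: the logit of choosing metformin equals m, and log HOMA-IR at week 146 is lowered by 0.1m. Ranges cover the eight scenarios and were re-run for this write-up.

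| User minus pooled non-user, HOMA-IR units | Random choice | With assumed motivation |
|---|---|---|
| Level at week 146 | +0.47 to +0.79 | +0.14 to +0.45 |
| Change, week 73 to 146 | −0.33 to −1.20 | −0.70 to −1.49 |
| Change, week 0 to 146 | +0.13 to +0.24 | −0.05 to −0.24 |

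The share w is 37–61%. Positive values mean users look worse.

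**4. A second model including BMI-SDS** (assumed mean BMI-SDS 3.0, SD 0.45; median HOMA-IR 3.4 to 5.0; 50% uptake; no drug effect; motivation effect 0.1 per SD). User minus pooled non-user at month 36 is +0.08 to +0.11 BMI-SDS and +0.21 to +0.35 ln HOMA-IR. On change from month 18 it is about −0.06 BMI-SDS and −0.20 to −0.27 ln HOMA-IR. With motivation switched off, the BMI-SDS change contrast is about zero, while the ln HOMA-IR one stays at −0.14 to −0.21. In this model regression to the mean is therefore a HOMA-IR matter.

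**The case against.** **The bias is already admitted.** The limitations section calls part 2 the major limitation, restates the eligibility rule, hedges the direction and promises to allow for it. For participants who are still eligible and may choose, overestimation is the expected direction: with the assumed motivation effect, users minus eligible decliners is −0.37 to −0.51 HOMA-IR units. This stands. The statement is incomplete, not wrong, because it covers the term U − D and omits w(D − R).

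**The reversal depends on the outcome scale.** A reader might infer that the stated direction is simply backwards. The documents do not support that. The primary endpoint is worded as a reduction, and the article does not fix levels, change from end of part 1 or change from baseline for part 2. Change from end of part 1 favours metformin, as the article says. Change from week 0 is only slightly affected and switches sign with modest motivation. Only unadjusted levels stayed reversed in every no-effect scenario run.

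**Restriction does not remove all bias.** A reader might infer that comparing eligible participants only gives an unbiased answer. In a simulation with random choice it does so by construction; with motivated choice it does not.

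**Visit frequency.** The Design section says "Participants using Metformin will visit the hospital six times, participants not using medication will have three hospital visits and three phone calls", and a reader might infer extra dietary counselling for users. Table 2 marks the users' extra visits (weeks 86, 110, 134) only for adverse events and co-medication, and places the only part 2 diary at week 146. That inference is not supported and forms no part of this point.

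**A full analysis plan may add adjustment.** It may. But the four-group definition and the single-source bias statement are fixed in this text.

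**Conclusion.** The point holds. As written, the four-group comparison sets participants who all still meet both criteria against a mixture, and the mixing variable is the outcome. The selection follows from the article's own allocation rule and needs no assumption beyond participants no longer meeting the criteria having, on average, different later values from those who do.

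Its size does rest on assumptions, because the article gives no recovery rate, uptake, within-person correlation or HOMA-IR spread. On the inputs above with random choice, the spurious differences are about +0.5 to +0.8 HOMA-IR units on level, −0.3 to −1.2 on change from end of part 1 and +0.1 to +0.2 on change from week 0, against a planning difference of 1.6. The effect on dichotomous outcomes is reasoned, not simulated. The net direction for the four-group comparison is uncertain.

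This should be fixed, but it does not threaten the trial's main result: it touches the fourth objective and leaves the randomised 18-month comparison intact.

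**What to change.** 1. Compare metformin with no medication in part 2 only among participants who meet the continuation criteria at the end of part 1. Adjust for BMI-SDS and HOMA-IR at that visit, part 1 arm and site. Label the result observational, because motivation bias remains.
2. Report participants no longer meeting both criteria separately from those eligible who declined, within each part 1 arm (six groups instead of four).
3. Also report the 36-month comparison by randomised arm. Describe it as a comparison of starting strategies: placebo participants may start metformin in part 2, so it does not estimate the effect of part 2 drug use.
4. Add eligibility selection to the limitations section, and state that the net direction of bias in the four-group comparison is uncertain.

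**Cost.** This is wording in the analysis plan and a few sentences on limitations. Table 2 already schedules the physical examination and glucose tolerance test at weeks 73 and 146, so no visit or procedure changes. At the time of the article 13 of 60 included participants had finished part 1, so the change could be made before most part 2 data existed. The drawback is smaller groups. With 72 per arm, no dropout, r = 0.35 and c = 0.50, the part 2 contrast has 72 × 0.65 × 0.50 = 23.4 users and 23.4 decliners per arm, with 72 × 0.35 = 25.2 reported separately.

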### Safety and tolerability

Safety will be reported as the amount of cases in which hepatic and renal functions exceed safety limits. Tolerability will be reported as descriptive statistics of adverse effects in relation with the achieved dosage level.

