### Intervention

#### Metformin

After randomisation, all participants will receive either metformin 500 mg tablets or identical placebo tablets. Medication is given according to an increasing dosage regimen. In week 1, participants take 1 tablet daily. Every week, dosage increases with 1 tablet, reaching a maximum of 4 tablets in week 4. This maximum dose will be administered till the end of part 1.

In case the participant develops gastro-intestinal symptoms, dosage will be reduced to the last well-tolerated dosage. Participants will be asked to return remaining study medication every visit. Pill counts will be performed by a research assistant.

During the follow-up study, metformin will be administered according to the dosage regimen of part 1.

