### Secondary outcome measures

Secondary outcome parameters for safety of metformin treatment are hepatic and renal function tests, and concentration of vitamin B12. For tolerability, the number of adverse events (in relation to the achieved dose level) is the outcome parameter.

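### Tolerability is tabulated by achieved dose, which gastro-intestinal symptoms themselves lower, so for those events the table cannot be read as dose-response

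*Protocol article*

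**What the plan says.** Three parts of the protocol article bear on this.

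- **Dosing (Intervention, Metformin).** Both arms escalate with identical tablets: "Every week, dosage increases with 1 tablet, reaching a maximum of 4 tablets in week 4". The dose then responds to symptoms: "In case the participant develops gastro-intestinal symptoms, dosage will be reduced to the last well-tolerated dosage".
- **Outcome (Secondary outcome measures).** "For tolerability, the number of adverse events (in relation to the achieved dose level) is the outcome parameter".
- **Analysis (Safety and tolerability).** "Tolerability will be reported as descriptive statistics of adverse effects in relation with the achieved dosage level".

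The article does not say whether achieved dose means the final dose, the highest dose reached or the dose at event onset. The tests of metformin against placebo stand under Efficacy of metformin; the safety and tolerability paragraph names no comparison by arm.

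On laboratory safety, the outcome section says: "Secondary outcome parameters for safety of metformin treatment are hepatic and renal function tests, and concentration of vitamin B12". The analysis paragraph says: "Safety will be reported as the amount of cases in which hepatic and renal functions exceed safety limits". Table 3 schedules vitamin B12 at seven visits (weeks 0, 25, 49, 73, 98, 122 and 146).

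**The concern.** Achieved dose is measured after randomisation, and for gastro-intestinal events it is changed by the outcome. A participant with symptoms moves down; one without symptoms goes to 4 tablets and stays there. Grouping by achieved dose therefore sorts participants partly by whether they had the event. The pattern across groups then says little about what the dose does.

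This is a stated method, fixed in both the outcome definition and the analysis paragraph, and not merely a detail left open. Safety and tolerability are the secondary objective. The article gives the lack of an evidence-based regimen for this age group as a motive, and it intends safety endpoints to feed models that lead to individualised dosing. The limitations section expects firm conclusions on 36-month tolerability. A table in which the top dose looks best tolerated could mislead on these points. The double-blind part 1 offers an unbiased contrast between arms that the tolerability paragraph does not use.

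**Working it through.** The plan states no figure here to reproduce, and the article gives no adverse event rates. Every rate below is an assumption used to show how each reading of achieved dose behaves.

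**1. Final dose.** Suppose the rule is followed and doses are not raised again. A participant ends below 4 tablets only after a gastro-intestinal event, and one who has such an event does not end on 4. The contrast between groups restates the rule and measures nothing.

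A simulation of 400,000 participants over 78 weeks makes this visible. It assumes one tablet up each week to 4, one tablet down after an event, and no re-escalation.

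- With a true dose effect (individual tolerance threshold with mean 5 and SD 1.5 tablets), 74.7% end on 4 tablets and 16.3% on 3.
- With no dose effect (0.3% risk per week at every dose), 79.1% end on 4 tablets and 17.9% on 3.

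In both cases the events sit in the lower groups, so the table cannot tell the two situations apart.

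**2. Highest dose reached.** Let p be a constant weekly risk, so dose has no effect. Reaching 4 tablets in week 4 requires three event-free weeks: (1 − p)^3.

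- p = 0.05: 0.95^3 = 0.857, so 86% reach 4 tablets.
- p = 0.10: 0.90^3 = 0.729, so 73% reach 4 tablets.

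Those held lower have had an event by definition. In the top group only week-4 events count during titration, that is 5% or 10%. The tilt is again towards low doses although dose does nothing. The top group also collects events after week 4, so the contrast shrinks over part 1, and for counts of events its direction is not fixed.

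**3. Dose at onset.** Same simulation with the true dose effect. The rate is the share of participants with an event at a level, divided by mean person-weeks at that level. Person-weeks are the first week at the level plus the later weeks of those who remain there.

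| Tablets | Risk in first week at level | Share with event at level | Person-weeks per participant | Rate per 100 weeks |
|---|---|---|---|---|
| 1 | 0.4% | 0.004 | 1 + 0.019 × 76 = 2.44 | 0.16 |
| 2 | 1.9% | 0.019 | 0.996 + 0.068 × 75 = 6.10 | 0.31 |
| 3 | 7.1% | 0.068 | 0.977 + 0.163 × 74 = 13.04 | 0.52 |
| 4 | 17.8% | 0.163 | 0.908 + 0.747 × 74 = 56.19 | 0.29 |

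With no dose effect the rates are flat, at 0.31, 0.30, 0.30 and 0.30. Onset attribution therefore does not create a false reversal. It does understate the top level, because those who cannot tolerate 4 tablets leave it and the tolerant contribute most of the time there.

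**4. By arm.** Both arms follow the same tablet schedule, so placebo participants also have an achieved dose. The text does not say whether the dose table separates the arms. Randomised arm is not altered by symptoms, so a comparison by arm avoids all three problems in part 1.

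**5. Vitamin B12.** Set side by side, the outcome section lists hepatic function, renal function and B12, while the reporting sentence lists hepatic and renal limits. The pharmacokinetics section mentions safety endpoints in its models without naming B12.

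**The case against.** The strongest reply is that the article never defines achieved dose, plans only descriptive statistics, and tests no dose-response. Describing which dose was reached and with what adverse effects is a legitimate account of tolerability under titration. The mechanism is also limited: only gastro-intestinal symptoms trigger the reduction rule. The adverse event form records dose adjustment as a possible action for any event, but no rule links other event types to a lower dose. And a journal article often leaves adverse event tables by arm to fuller documents.

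Much of this stands. It confines the problem to gastro-intestinal events and to interpretation, and it means the lack of a stated comparison by arm should not be read as a decision to omit one. It does not remove the point, because outcome and analysis are both tied to a variable that the event changes.

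Two stronger readings are tempting. A reader might infer that the dose-event relation is reversed by construction, with every event at low doses and none at the top. That follows only from a final-dose reading, where it repeats the rule, and the documents do not fix that reading. A reader might also infer that vitamin B12 will have no analysis. The documents show only that a two-sentence summary does not mention it.

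A fair objection to the remedy is that a table by dose at onset is also distorted, as step 3 shows. That is accepted, and it is why the comparison by arm should lead.

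**Conclusion.** The point holds in limited form. For gastro-intestinal events, a table by final or highest achieved dose concentrates participants with events in the lower-dose groups whatever the true dose effect, and it should not be read as dose-response. Reversal is certain only if achieved dose means final dose, the rule is followed and doses are not raised again. Under the highest-dose reading the tilt is present during titration and weaker later. Under dose at onset there is no spurious reversal, but the top level is diluted. The size in this trial is unknown; the percentages and rates above rest on assumed risks.

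The change is worth making because the alternative is better and cheap. The vitamin B12 mismatch is a minor alignment and would not justify a comment alone.

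**What to change.** - Make metformin versus placebo as randomised the main part 1 tolerability analysis: participants with at least one event and events per person-time, with the risk difference and 95% CI.
- Report dose reductions and the dose reached, by arm, as a tolerability outcome in its own right.
- Define achieved dosage level. Give any dose table by dose at event onset with person-time at that level, separately for both arms. Label it descriptive, because intolerant participants leave the higher levels.
- Name vitamin B12 by arm in the safety reporting, to match the declared outcome.

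No dosing rule needs to change. The cost is wording and slightly more programming. The listed adverse event items do not include tablets taken at onset, so that dose must be derived from event start dates, the recorded action on study medication and pill counts. Pill counts are made only at visits, so some onset doses will be approximate.

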### Pharmacokinetics

All observed metformin plasma concentrations will be analysed using nonlinear mixed effects modelling to develop a population pharmacokinetics/pharmacodynamics (PK/PD) model. Using this modelling approach, infrequently obtained samples and observations in the clinical situation can be utilized to analyse determinants of variability in drug response
[32-34]. In both the population PK (drug concentrations) and PD (efficacy and safety endpoints) models, the influence of age, bodyweight, BMI, percentage of body fat, gender, Tanner stage, and genetic constitution will be evaluated resulting in individualized dosing regimens. In addition to demographic parameters, the influence of genetic variation in the SLC47A1 gene, which may play an important role in the pharmacokinetics of metformin, is studied
[35-37]. If other relevant genes are discovered during the metformin study, these genes will also be determined.

